## Abstract

**Background:**

Patients with stroke are at a high risk for long-term handicap and disability. In the first weeks after stroke muscle wasting is observed frequently. Early post-stroke rehabilitation programs are directed to improve functional independence and physical performance. Supplementation with essential amino acids (EAAs) might prevent muscle wasting and improve rehabilitation outcome by augmenting muscle mass and muscle strength. We aim to examine this in a double blinded, randomized placebo-controlled clinical trial.

**Methods:**

Patients with ischemic or haemorrhagic stroke will be enrolled at begin of the early post-stroke rehabilitation in a parallel group interventional trial. Oral supplementation of EAAs or placebo will be given for 12 weeks in a double blinded manner. Physical and functional performance will be assessed by exercise testing before supplementation of EAAs as well as at discharge from the in-patient rehabilitation, at 12 weeks and 1 year afterwards.

**Discussion:**

This is the first randomized double-blinded placebo-controlled clinical study aiming to assess the effect of the EAAs supplementation on muscle strength, muscle function and physical performance in stroke patients during early post-stroke rehabilitation. Supplementation of EAAs could prevent muscle mass wasting and improve functional independence after stroke.

**Trial registration:**

The study is registered at the German registry for clinical trials as well as at World Health Organization (WHO; number DRKS00005577).

## Background

Long-term disability and functional dependency are the main complications after stroke. Impaired skeletal muscle innervation due to damage results in the degeneration of motor units, paresis, and immobility accompanied by skeletal muscle atrophy [1–4]. Notably, loss of muscle mass and muscle function, defined as sarcopenia, have been originally described as a phenomenon of aging [5]. However, muscle wasting observed in stroke patients is a disease-related phenomenon and the term ‘stroke-related sarcopenia’ has been suggested [1]. The aetiology of sarcopenia is multifactorial [6]. This is also true for stroke-depended sarcopenia. Several pathophysiological mechanisms including metabolic imbalance, inactivity, malnutrition, and inflammation may contribute to the reduction of muscle mass after stroke [7, 8]. Stroke-related muscle wasting is accompanied by body weight loss, neuro-hormonal activation, and a systemic shift towards catabolic over-activation [8]. In addition, activation of catabolic pathways in the skeletal muscle of the paretic and non-paretic limbs has been observed in experimental stroke [9].

Early rehabilitation has a great impact on the functional recovery after stroke. A previous study showed that 80 % of the patients achieve best functional recovery within 6 weeks after stroke, and after 12.5 weeks 95 % of all stroke patients completed their functional recovery [10]. However, one year after stroke more than 30 % of the patients remained functionally dependent [11].

Skeletal muscles play a central role in post-stroke rehabilitation. The goal of rehabilitation is to restore functional muscle capacity and to prevent long-term disability. Therefore, prevention of muscle wasting, increasing muscle strength, reactive development of novel neuromuscular junctions, and stabilisation of the catabolic-anabolic imbalance are primary aims of post-stroke rehabilitation.

Nutritional intervention may contribute to the improvement of muscle bulk and functional capacity in the early post-stroke rehabilitation. Thus, a beneficial effect of dietary supplementation of essential amino acids (EAAs) has been shown for an improvement of skeletal muscle mass and function in the elderly [12, 13]. Availability of EAAs is regarded as a limiting step in the synthesis of new muscle proteins [14]. Previously it has been shown that supplementation of EAAs in the elderly was responsible for amino acid-induced stimulation of muscle protein anabolism [15]. Therefore, an individually adjusted rehabilitation program that includes physical, functional and neuropsychological training as well as dietary supplementation of the EAA might provide the best rehabilitation outcome. Thus, in the present clinical trial the following hypotheses will be tested:Oral uptake of EAAs restores skeletal muscle function and physical performance;Oral uptake of EAAs contributes to physical independence and enhances the effectiveness of post-stroke rehabilitation;Availability of EAAs reduces muscle wasting after stroke.

We aim to demonstrate that nutritional supplementation with biologically limited available EAAs (l-leucine, l-lysine, l-isoleucine, l-valine, l-threonine, l-cystine, l-histidin, l-phenylalanine, l-methionine, l-tyrosin, and l-tryptophane), in synergy with individually adjusted physical training prevent muscle wasting after stroke and improve the effect of post-stroke early rehabilitation.

## Methods

### Study design

The “Influence of essential amino acids on muscle mass and muscle strength in patients with cerebral stroke during early rehabilitation (AMINO-Stroke)” study is a randomized double-blinded placebo controlled interventional clinical trial. The study is planed as a monocentric trial within the interdisciplinary trial programme of the Center for Stroke Research Berlin (CSB) and is funded by the German Federal Ministry of Education and Research (BMBF; grant number CSB 01EO1301). The study has been approved by the Brandenburg Ethics Committee for the recruiting site (S13(a)/2013) and is conducted in accordance with the Declaration of Helsinki. The study is registered at the German registry for clinical trials as well as at World Health Organization (WHO; number DRKS00005577).

### Patient eligibility

Patients admitted to the rehabilitation centre Brandenburg Klinik, Bernau, Germany within 8 weeks after ischemic or haemorrhagic stroke will be screened for the eligibility. Patients of both genders, aged 45 years or older will be informed about the study. After obtaining of written informed consent from the patients they will be randomized 1:1 to intervention and control group by a web-based online randomization procedure provided by the Pharmacy at the Charité. For inclusion and exclusion criteria see Table 1.

**Table 1 Tab1:** Inclusion and exclusion criteria of the AMINO-Stroke

Inclusion criteria:
• Patient >45 years
• Patients with ischemic or haemorrhagic stroke within 8 weeks to enrolment
• Brain magnet resonance imaging or computer tomography demonstrating stroke
• Motoric disability of an upper and /or lower limb (Rivermead Motor Assessment Gross Function > 1 and <11)
• Signed informed consent
Exclusion criteria:
• Clinically significant findings on physical examination or presence of clinically significant disease that would interfere with study evaluation in the opinion of the treating physicians
• Participation in another clinical trial investigating a nutritional product
• History of intolerance or allergic response to similar nutritional products or known hypersensitivity to essential amino acids
• Clinical sighs and symptoms of infection requiring antibiotic therapy at the time of enrolment that prevent completion of trial-related assessments as judged by the investigator
• Transaminases (AST or ALT) > 3 times the upper limit of normal (ULN)
• Severe renal dysfunction or nephrotic syndrome
• Acquired immunodeficiency syndrome, HIV or Hepatitis C infection
• Current therapy with anabolic steroids or appetite stimulants
• Current immunosuppressive therapy, heart transplantation, or renal dialysis
• Life expectancy < 6 months

### Planned clinical follow-up visits

In order to evaluate an effect of the EAAs on muscle function, baseline functional assessment program will be performed at admission, followed by follow-up assessment at discharge from the in-patient rehabilitation (Table 2). All patients included into the study will receive 12 weeks either the EAAs (4 gram, 3 times a day) or placebo dissolved in a glass of water as a drinking solution.

**Table 2 Tab2:** Functional assessment at baseline and during follow-up

Extended functional assessment at baseline and at 4 weeks follow-up
• Activity of daily living (modified Rankin scale, Barthel Index)
• Functional assessment scales and physical performance (Rivermead Motor Assessment Gross Function, Fugl-Meyer Scale, Functional ambulatory capacity)
• Muscle functional assessment (SPPBT, hand grip, pinch grip)
• Quality of life and nutritional status (EQ-5D, PGA)
• Blood and biomarker bank: metabolic /immunologic profile
• 24 h Holter electrocardiogram (ECG)
• Body composition by bioelectrical impendance analysis (BIA)
• Urine status
Functional assessment at 3 and 6 months follow-up
• Activity of daily living (mRS, Barthel index)
• Muscle functional assessment (SPPBT, hand grip, pinch grip)
• Quality of life and nutritional status (EQ-5D, PGA)
• Blood and biomarker bank: metabolic/immunologic profile
• 24 h Holter ECG
• Body composition by bioelectrical impedance analysis (BIA)
• Urine status

Two weeks after the enrolment a study nurse visit for evaluation of compliance of the EEAs supplementation and tolerance to the compound is planned. After discharge from the in-patient rehabilitation, two follow-up visits at 3 and at 12 months are planned. Patients will be tested for functional performance and physical independence during a 1-day ambulatory visit. Patients, who are unable to visit the study centre will be contacted by telephone and interviewed using a standardised questionnaire. The study design is summarized in Fig. 1.

**Fig. 1 Fig1:**
[figure not shown]
Overview of the AMINO-Stroke study

### Outcomes and endpoints

#### Primary outcomes

Primary outcomes will be assessed at the 4 week follow-up visit. Primary endpoints include:Physical performance according to the Rivermead motor assessment (RMA) *gross function* scale;Muscle strength in a maximum hand grip strength test.

#### Secondary outcomes

Secondary endpoints include:Functional outcome assessed by Barthel Index (BI);Quality of life assessed according to EuroQoL (EQ)-5D (EQ-5D) questionnaire at 3 and 12 months follow up visits;Muscle function and motor capabilities assessed by pinch grip strength test, motor assessment scale, Fugl-Meyer Score (motor functional domain), Functional ambulatory capacity and short physical performance battery test;Changes of body composition assessed by bioelectrical impedance analysis (BIA);Changes in insulin sensitivity;Changes of nutritional status according to Mini Nutritional Assessment questionnaire and metabolic profile according to biochemical analyses;Rate of post-stroke complications, stroke –associated infections and re-hospitalization for any reason;Safety and tolerability of EEAs supplementation.

#### Physical examinations

*Rivermead motor assessment (RMA) gross function scale* comprised a series of 13 questions, and covers a range of activities from turning over in bed to hop on affected leg five times [16, 17]. *Hand grip strength* [18] *and pinch grip tests measures* muscle isometric strength. The maximum value of three measurements will be evaluated [19]. *Motor assessment scale (MAS)* includes nine items scoring from 0 to 6, and is designed to assess eight areas of motor function, balance, and muscle tone [20]. *Fugl-Meyer scale* is a system for the evaluation of motor function, balance, sensory qualities, and joint function in hemiplegic patients. This system applies a cumulative numerical score [21, 22]. *Functional Ambulation Category (FAC)* includes six categories ranging from 0 to 5 and is defined by ability of the patient to ambulate, with a lowest score 0 for “patient cannot ambulate” to 5 “patient can ambulate independently” [23].

#### Functional independency assessment

*Barthel index (BI)* will be used for the assessment of functional independence. BI includes 10 basic aspects of activities related to self-care and mobility with scores of 0–100, where the lower scores indicate greater dependency [24]. *Short physical performance battery test (SPPBT)* includes examination of ability to stand with the feet together in the side-by-side, semi-tandem, and tandem positions, time to walk 3 or 4 meters, and time to rise from the chair and return to the seated position 5 times [25].

#### Nutritional status and quality of life

*Mini Nutritional Assessment (MNA)* is a simple scale to measure nutritional status [26]. A score above 24 points identifies patients with a good nutritional status, whereas a score below 17 points reveals patients with malnutrition. *Subjective Global Assessment (SGA)* assesses nutritional status based on features of the history and physical examination [27]. *EQ-5D questionnaire* is an instrument for the generic measurements of health-related quality of life, comprising a Visual Analogue Scale for self-rating of general health and five domains evaluating mobility, self-care, usual activities, pain/discomfort, and anxiety/depression [28]. A score of 1 is the best possible general health status in each case; the dimensions may also be expressed as percentage of patients scoring from 1 to 3 (best to worst health status) or percentage of patients with ‘any’ complaint (scoring 2 or 3 in each domain) [29].

#### Body composition analysis

Body composition analysis at baseline and follow-up visits will be assessed by BIA device (BodyStat QuadScan 4000, Bodystat Limited, British Isles). The BIA device measures resistance (*R*), reactance (*Xc*) and phase angle (*φ*). The measurements will be performed in patients in supine position lying on a non-conducting surface with arms slightly abducted from the trunk and legs slightly separated, after resting at least for 20 min [30]. Surface electrodes will be placed on the dorsal surface of hand and foot of the similar side. Skeletal muscle (SM) mass will be estimated according to the equation of Baumgartner at all [31].

#### Serum biomarker assessment

Blood samples and urine status will be assessed at admission and discharge from the inpatient rehabilitation as well as at follow up visits for routine clinical parameters, inflammatory and metabolic markers, and safety analyses (liver and kidney function).

### Sample size calculation and statistical analyses

A total of 110 patients is planned to be enrolled in the study. A prospective sample size calculation has been performed based on observational data from our study centre. A sample size of 55 in each group will have 80 % power to detect a clinically relevant difference in Rivermead Motor Assessment Gross Function scale improvement between the groups of 1.5 points and a clinically relevant improvement of handgrip strength. The analysis of primary endpoints will use the principle of intention- to-treat. The carry-forward principle will be adopted for unavailable or missing data. Treatment effect will be assessed by unpaired comparison of both treatment arms for the change from baseline using the Student t-test. A significance level of α < 0.05 will be specified to indicate statistical significance. Secondary endpoints will be analyzed using standard statistical methods. For safety endpoints Chi-squared test of Fisher’s Exact test will be used for event rates (e.g., death, re-stroke, hospitalization, cardiovascular event)

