## Discussion

The present AMINO Stroke study will be the first randomized double-blinded trial investigating an effect of essential amino acids (EAAs) on skeletal muscle functional capacity, muscle mass, muscle strength and physical performance in early post-stroke rehabilitation. In addition, the effect of EAAs supplementation on stroke-related quality of life, nutritional status, activities of daily life and outcome will be evaluated.

An improvement of physical and functional performance in stroke patients is expected after participating in 4-weeks rehabilitation program [32]. In the present study we expect a beneficial impact of the dietary supplementation of the EAA on skeletal muscle function and muscle mass during post-stroke rehabilitation.

The benefit of EAAs supplementation on skeletal muscle has been shown in several studies in elderly individuals. Thus, an elevated level of muscle protein synthesis was dependent on the availability of EAAs in a dose-depended manner [33]. An experimental study performing in the young adults revealed an increase of leucine incorporation into the skeletal muscle proteins under administration of EEAs as a flooding dose [34]. Ingestion of EAAs shortly after exercise enhanced muscle protein synthesis in older adults, indicating a combination of EAAs with exercising as a sufficient therapy for the treatment of muscle wasting [35]. Another study showed an improvement of lean mass, muscle functional capacity and muscle strength after 16 weeks supplementation of EAAs and arginine in healthy elderly individuals [36].

A reduction of the muscle mass might be directly depending on a limited availability of the EEAs and other nutrients [14]. Impaired feeding which results in malnutrition is frequently observed in patients with dysphagia after stroke [37]. About 50 % of stroke patients have feeding difficulties due to dysphagia [38]. In older patients reduced nutritional status might be observed already at hospital admission with the diagnosis of acute stroke [39]. Patients with lower body weight have been observed to have worse fatal and non-fatal outcome after stroke [40]. While the inverse association of overweight and improved outcome has previously been termed obesity paradox [41], the perception advanced towards an obesity paradigm, acknowledging the protective overweight in cardiovascular disease [42].

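### Carrying forward a missing 4-week primary result scores the patient as exactly no change, which attenuates a true effect and, if dropout differs between arms, distorts it in either direction

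*Protocol article*

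**What the plan says.** Under Sample size calculation and statistical analyses, the protocol article sets three rules for the primary endpoints in consecutive sentences:

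- Population: "The analysis of primary endpoints will use the principle of intention- to-treat".
- Missing data: "The carry-forward principle will be adopted for unavailable or missing data".
- Test: "Treatment effect will be assessed by unpaired comparison of both treatment arms for the change from baseline using the Student t-test".

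Under Primary outcomes, the two endpoints are RMA gross function and maximum hand grip strength, and "Primary outcomes will be assessed at the 4 week follow-up visit". Table 2 (Planned clinical follow-up visits) places RMA under "Extended functional assessment at baseline and at 4 weeks follow-up" and not in the list for later visits. Hand grip is in both lists. The one contact between baseline and 4 weeks is described as "Two weeks after the enrolment a study nurse visit for evaluation of compliance" and of tolerance; no RMA or grip test is listed for it.

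The Discussion states the expected course: "An improvement of physical and functional performance in stroke patients is expected after participating in 4-weeks rehabilitation program".

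**The concern.** Carry-forward needs an earlier value to carry. For a missing 4-week RMA or grip result the only earlier value is baseline, so the change entered into the t-test is exactly 0. That is an assumption about the patient's course, and it conflicts with the improvement the article expects on average in both arms. The Background adds that 80% of patients reach best functional recovery within 6 weeks of stroke. Eligibility requires a baseline RMA above 1 and below 11 on a 13-item scale, so there is room to improve.

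Both primary comparisons are at stake. Each arm's mean change is pulled towards zero in proportion to its share of missing patients. If the shares are alike, a real difference is diluted. If they differ, for example because one drink is tolerated less well, the rule itself produces part of the observed difference.

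**Working it through.** **The plan's own figure.** The article gives 55 per arm, 80% power and a 1.5-point RMA difference, but no SD. The sample size therefore cannot be reproduced independently; only the implied SD can be found. Assuming a two-sided 0.05 level:

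- Normal approximation: SD = 1.5 / [(1.960 + 0.842) × √(2/55)] = 1.5 / 0.534 = 2.81.
- Noncentral t: SD = 2.78, used below. It returns 80% power with no missing data.

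**Inputs.** From the article: n = 55 per arm, difference 1.5, t-test on change. Assumed: SD of change 2.78, mean gain 2 points on control (so 3.5 on active), the missing shares shown, and missingness completely at random within arm.

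**Formulae.** For missing share m, true mean change μ, and missing change set to 0:

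- arm mean = (1 − m)μ
- arm variance = (1 − m)SD² + m(1 − m)μ²
- SE of the difference = √[(variance control + variance active) / 55]

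The comparator is the same t-test on observed patients only, with 55(1 − m) per arm. Under the same assumptions its expected difference stays at 1.5.

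**Worked case, 10% missing per arm.** Difference = 0.9 × 3.5 − 0.9 × 2 = 3.15 − 1.80 = 1.35. Variances: control 0.9 × 7.728 + 0.09 × 4 = 7.316; active 0.9 × 7.728 + 0.09 × 12.25 = 8.058. SE = √(15.374 / 55) = 0.529. Power is 72%.

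**True difference 1.5**

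| Missing, placebo / active | Carry-forward estimate | Power | Observed-data estimate | Power |
|---|---|---|---|---|
| 5% / 5% | 1.43 | 76% | 1.5 | 78% |
| 10% / 10% | 1.35 | 72% | 1.5 | 76% |
| 20% / 20% | 1.20 | 63% | 1.5 | 71% |
| 5% / 15% | 1.08 | 51% | 1.5 | 76% |
| 15% / 5% | 1.62 | 87% | 1.5 | 76% |

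The unequal rows are 0.85 × 3.5 − 0.95 × 2 = 1.075 and 0.95 × 3.5 − 0.85 × 2 = 1.625.

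**No true difference (both arms gain 2 points)**

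- Equal missingness: difference 0, two-sided rejection 5%.
- 5% placebo / 15% active: 0.85 × 2 − 0.95 × 2 = −0.2, two-sided rejection about 6.7%.
- 15% placebo / 5% active: +0.2, also about 6.7%.

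**Sensitivity to the assumed gain.** For control gains of 1 to 4 points, power at 10% missing per arm runs from 74% down to 65%, and at 20% from 67% to 51%. Under the null with 5% against 15% missing, the spurious difference is 0.1 to 0.4 points and two-sided rejection 5.4% to 11.1%.

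The zero-change mechanism is the same for hand grip. The article gives no grip difference or SD, so no figures are offered for it.

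**The case against.** The best defence is that the effect may be small. The Planned clinical follow-up visits section sets the follow-up assessment at discharge, and the Discussion puts the early rehabilitation phase at about 4 weeks, so most patients should still be on site. At 5% missing per arm the estimate is 1.43. Much of the equal-dropout power loss also comes from missing data as such: at 10% missing, power falls from 80% to 76% with observed data and to 72% with carry-forward, so the rule accounts for about 4 points, and for about 8 at 20%. Improvement is expected on average; for a patient lost through re-stroke or infection, zero may be right or even optimistic. All of this stands. It limits the size but does not justify one fixed value for everyone with a missing result.

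Four stronger readings are tempting and are not supported:

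- **That the rule favours the product.** With more loss on active it works against the product: in the 5% / 15% null case, false benefit falls from 2.5% to about 1% and false harm rises to about 5.8%. False benefit becomes more likely only with more loss on placebo.
- **That scores are carried past death.** The article lists death only among safety event rates and does not say how a death enters an efficacy endpoint.
- **That early values stand in for long-term results.** The article says "Patients, who are unable to visit the study centre will be contacted by telephone and interviewed using a standardised questionnaire", and grip, the performance battery and bioimpedance cannot be measured by telephone. These are secondary endpoints at that stage, however, and the article assigns secondary endpoints to standard methods in a separate sentence. Whether carry-forward applies to them is unclear.
- **That the standard errors are wrong.** The t-test estimates the variance of the filled-in data, and its 5% rejection under the null with equal dropout agrees with that. The fault lies in the quantity estimated.

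**Conclusion.** The point holds for 4-week RMA and hand grip. Carry-forward is written down as the chosen rule, so it is not a detail left to a fuller document, and the visit schedule turns it into zero change for each missing patient. This treats the discharge and 4-week assessments as one visit, as the article indicates.

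With similar dropout a true effect is attenuated by the missing share: 1.5 points becomes 1.43, 1.35 or 1.20 at 5%, 10% or 20%. With unequal dropout the distortion can go either way and type I error can exceed 5%. With equal dropout and no true effect there is no bias. The proportional shrinkage at equal dropout follows from the rule when missingness is completely at random within arm; the power figures and the unequal-dropout results also depend on the assumed SD, control gain and missing shares, none of which the article gives.

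**What to change.** - Replace carry-forward as the primary method for 4-week RMA and hand grip with a baseline-adjusted analysis valid under missing at random, for example ANCOVA with multiple imputation by arm using baseline variables already collected.
- Keep carry-forward as a labelled sensitivity analysis, beside a delta-shift analysis that makes the imputed changes progressively less favourable.
- Attempt the 4-week RMA and grip assessment in all randomised patients, including those who have stopped the product.
- If carry-forward is also meant for later secondary endpoints, say so, and state that it does not extend past death.

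The cost is modest programming, a change of wording, and some follow-up effort at a visit that is already planned. The new primary analysis rests on missing at random, which the data cannot confirm; the delta-shift analysis shows how far the conclusion depends on it.

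### The primary t-test on change from baseline is valid but fixes the baseline coefficient at 1 and ignores time since stroke; a baseline-adjusted linear model would be at least as precise at almost no cost

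*Protocol article*

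**What the plan says.** The section on sample size and statistical analyses of the protocol article names the primary method: "Treatment effect will be assessed by unpaired comparison of both treatment arms for the change from baseline using the Student t-test". It sets the significance criterion ("A significance level of α < 0.05 will be specified to indicate statistical significance") and justifies the numbers: "A total of 110 patients is planned to be enrolled in the study", and "A sample size of 55 in each group will have 80 % power to detect a clinically relevant difference", namely "Rivermead Motor Assessment Gross Function scale improvement between the groups of 1.5 points" together with "a clinically relevant improvement of handgrip strength". It gives no SD, no correlation between baseline and 4 weeks, and no figure for grip.

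The article names no covariate, adjusted model or stratification factor; under Patient eligibility, allocation is described only as 1:1 through a web-based procedure.

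The variables needed for adjustment are already to hand:
- Table 2 lists RMA gross function and hand grip at both baseline and 4 weeks, the time point of the primary outcomes.
- Table 1 restricts entry by time since stroke ("Patients with ischemic or haemorrhagic stroke within 8 weeks to enrolment"), so that time must be known for every patient.
- Table 1 also restricts entry RMA to above 1 and below 11. Under Physical examinations, the scale is said to have 13 items.

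**The concern.** A change score subtracts the baseline value with a coefficient of exactly 1. That is the best choice only if the regression slope of the 4-week value on baseline is itself close to 1. Two features of this trial make it doubtful that the change score captures what is known at entry.

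- **The scale is bounded.** A patient entering at 2 can gain up to 11 points (13 − 2), and one entering at 10 can gain only 3 (13 − 10). Change is then likely to depend on baseline, which means a slope different from 1.
- **Entry is spread over the recovery period.** The Background cites a study in which 80% of patients "achieve best functional recovery within 6 weeks after stroke", while entry is allowed up to 8 weeks. On the protocol's own account, some patients may enter while recovering fast and others near their plateau. Subtracting baseline does not remove that difference.

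Whatever baseline and time since stroke explain, and the change score does not capture, stays in the error term. At stake is precision: a wider confidence interval and less power than the same 110 patients could give.

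**Working it through.** **Inputs from the document:** 55 per arm, 80% power, 1.5-point difference in RMA improvement, α 0.05. **Assumed:** two-sided test, no dropout allowance, and the stated power taken as correct.

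**1. The plan's own figure.** With no SD stated, 55 per arm can be neither confirmed nor refuted. Solving backwards with the normal approximation:

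SD of change = 1.5 / [(1.960 + 0.842) × √(2/55)] = 1.5 / (2.802 × 0.1907) = 2.81.

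The noncentral t gives 2.78, a standardised effect of 1.5/2.78 = 0.54. The variance of change is 2.78² ≈ 7.74 and the standard error of the treatment difference is 2.78 × 0.1907 = 0.53. Other readings move the implied SD: 3.16 if one-sided, 2.55 if α is halved for two endpoints, and 2.66 to 2.51 if 10–20% dropout was already allowed for.

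**2. Formulas.** Let s be the baseline SD, k the ratio of 4-week to baseline SD, r the correlation, and β = rk the slope of the 4-week value on baseline.
- Variance of change = s²(1 + k² − 2rk)
- Residual variance after baseline adjustment = k²s²(1 − r²)
- Difference between them = s²(1 − β)²

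The difference is a square, so large-sample adjustment cannot lose precision. It is zero only when β = 1.

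**3. What the entry range allows.** Scores spread evenly over the integers 2 to 10 have SD √((9² − 1)/12) = 2.58. The largest possible SD, with half the patients at 2 and half at 10, is 4.0. A baseline SD of 2.6 to 2.8 is therefore a reasonable assumption.

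**4. Power with 55 per arm.** The variance of change is held at 7.74, r is solved from s and k, and power is from the noncentral t with one degree of freedom spent.

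| Baseline SD | k | r | β | Variance ratio | Power |
|---|---|---|---|---|---|
| 2.6 | 0.9 | 0.37 | 0.33 | 0.61 | 94.8% |
| 2.6 | 1.0 | 0.43 | 0.43 | 0.71 | 91.2% |
| 2.6 | 1.2 | 0.54 | 0.65 | 0.89 | 84.3% |
| 2.6 | 1.4 | 0.65 | 0.91 | 0.99 | 80.3% |
| 2.8 | 0.9 | 0.46 | 0.41 | 0.65 | 93.5% |
| 2.8 | 1.0 | 0.51 | 0.51 | 0.75 | 89.8% |
| 2.8 | 1.2 | 0.61 | 0.73 | 0.92 | 83.0% |
| 2.8 | 1.4 | 0.70 | 0.99 | 1.00 | 80.0% |

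Example, s = 2.8 and k = 1: r = 1 − 7.74/(2 × 7.84) = 0.506; residual variance = 7.84 × (1 − 0.506²) = 5.83; ratio = 5.83/7.74 = 0.75.

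**5. Time since stroke.** The document does not say how much it explains. If it took up 5–10% of the remaining variance (assumed), power in the equal-SD rows would be about 91% to 94%. In the k = 1.4 rows, where baseline adjustment gains nothing, it would be about 82% to 84%.

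**6. Hand grip.** No effect size or SD is given, so nothing can be computed.

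**The case against.** The strongest defence is that nothing here is wrong. A two-sample t-test on change is valid in a randomised trial, keeps its type I error, and matches the improvement scale on which the sample size is stated. That stands in full. An analysis plan that is not shown may add adjusted analyses, but the article names the unadjusted test as the method for the treatment effect.

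Four stronger readings are tempting, and the document does not support them.

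- **That baseline RMA and grip are wasted.** They are used, with a fixed coefficient. Only time since stroke is unused.
- **That chance baseline imbalance goes uncorrected and biases the result.** Imbalance is subtracted, and when β is below 1 it is over-corrected, leaving (β − 1) × imbalance. With equal SDs of 2.6 to 2.8, a two-standard-error imbalance is about 1.0 to 1.1 points (2 × 0.1907 × SD) and shifts the estimate by about −0.5 to −0.6 points. This variation is already inside the t-test's standard error of 0.53. Averaged over randomisation it is imprecision, not bias.
- **That a change score is efficient only if baseline and follow-up correlate near 1.** The condition is a slope near 1. In the table, r = 0.70 with k = 1.4 gives β = 0.99 and no loss. Restricted entry could well push k above 1, while the 13-point ceiling pulls the other way; the document does not settle which.
- **That the gain can be read off for a typical correlation.** The equal-SD ratio (1 + r)/2 gives 86% power at r = 0.7 and 84% at r = 0.8. But with an SD of change of 2.78, the baseline SD would have to be 2.78/√(2 × 0.3) = 3.6 and 2.78/√(2 × 0.2) = 4.4. The second exceeds the maximum of 4.0, and the first needs almost all patients at the extremes.

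It is also fair to say that 8 weeks is an upper limit and not an observed spread, so the contribution of time since stroke may be small.

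**Conclusion.** The point holds as one of efficiency, not validity. The stated primary test fixes a coefficient that the data could estimate and omits a prognostic variable that must be known at entry. The protocol's own entry criteria and cited recovery pattern make it likely that both matter.

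The size is uncertain. About 90% power instead of 80% for RMA is the result if the SD of change is about 2.8 and the baseline and 4-week SDs are equal at about 2.6 to 2.8. The gain is larger if the 4-week SD is smaller than the baseline SD, and close to nil if it is about 1.4 times as large. These SDs are assumptions; the 2.8 itself is back-solved from the stated power. None of this shows that 110 patients is the wrong number or that the planned test would mislead. The case for changing it is that the possible gain is worthwhile and the downside negligible.

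**What to change.** Replace the sentence on the primary test with one that specifies, for each primary endpoint, a linear model of the 4-week value on treatment, the baseline value of that endpoint, and weeks from stroke to randomisation. Report the adjusted treatment difference with its 95% confidence interval. Keep the t-test on change as a supportive analysis, which preserves the link to the sample size statement.

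Fixing the covariates in advance also removes the temptation to choose an adjustment after seeing an imbalance. The sponsor can use its own observational data to check the SDs and correlation and so replace the assumed range above.

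The cost is one sentence of text and one or two degrees of freedom out of 108. No new data, visits or patients are needed.
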